### Study outcome and measurement

### 4.2.1 Primary outcome

Response to treatment will be classified according to WHO criteria (Appendix 3), using clinical (1996: ACR, ETF, LTF) and parasitological (S, RI/RII/RIII) classification systems, with slight modifications.1 In addition, patient outcomes will be classified using the newly proposed WHO classification system (2002: ACPR, ETF, LCF, LPF), for purposes of data reporting.2 The efficacy of the combination regimens will be assessed by comparing the proportion of patients with clinical treatment failure at 28 days. Clinical outcome will be dichotomised into success (ACR) and failure (ETF or LTF). Pair wise comparisons between regimens will be made on an intention-to-treat basis.

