### 7.3. Management of clinical treatment failures:

Patients who are classified as clinical failures (early or late treatment failure, Appendix 3) will be treated with quinine 10 mg/kg orally three times a day for 7 days. Any patient who develops evidence of severe malaria or danger signs during malaria follow-up, will be referred for appropriate treatment with parenteral quinine at the local facility or hospital. Any patient who responds clinically to treatment, but has a positive thick blood smear on day 28 (asymptomatic parasitaemia) will be treated with standard doses of oral quinine. Hemoglobin will be repeated on the day the patient is classified as a clinical treatment failure.

- 1. **Exclusion after enrolment and loss to follow-up:**

Patients will be excluded from the study after enrolment if any of the following occurs:

- 1. Use of antimalarial drugs outside of the study protocol.
  2. Development of concomitant febrile illness that may interfere with outcome classification.
  3. Withdrawal of informed consent.

Patients who fail to attend a follow-up visit and are unable to be located within 24 hours on Days 1-3 or within 48 hours on Days 4-28 will be considered lost to follow-up.

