### 8.2. Analytical plan:

Data analysis will be primarily performed by the project statistician using EPI INFO, SPSS ACCESS and STATA statistical software packages, with additional assistance from members of the UCSF Epi-Center in San Francisco and the University of California, Berkeley, Department of Epidemiology. Primary analyses will be conducted based on intention-to-treat and the primary analysis population will include all randomised subjects fulfilling selection criteria.

Descriptive statistics will be used to summarise baseline characteristics of study patients. Parasite density values will be normalised using logarithmic transformation. All dichotomous variables will be compared between treatment groups using chi-square tests or Fisher’s exact tests. Continuous variables will be compared using t-tests. A p-value of < 0.05 will be considered significant.

Because age is a strong effect modifier in malaria, an age-stratified subgroup analysis for efficacy outcomes is planned. Study subjects will be stratified by age (< 5 years and > 5 years) for analysis of treatment outcome including clinical outcome at 14 and 28 days, and parasitological outcome at 14 and 28 days. Results for the two age groups will be presented independently. After calculating an estimate of association for each of the two age groups, a single adjusted measure of risk difference will be calculated. Other factors that may impact on antimalarial treatment outcome include temperature4 and mean parasite density at presentation ([name], unpublished data). Because a randomised trial is planned, we anticipate that known and unknown confounding factors will be equally balanced between the treatment groups. If by chance, there is an imbalance between the treatment groups for one or more potential confounding variables, adjustment will be made using multiple logistic regression.

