**For exact definitions refer to:**

- Study Poster in Clinic
- Field Manual Appendix 3
- SOP # DATA3-003 CRF

| INCOMPLETE EFFICACY OUTCOME |
| --- |
|  **Excluded** - If yes, reason for exclusion: (Must tick one reason below)   Other antimalarial use: if yes, describe__________________________   Withdrew informed consent   Concomitant febrile illness: if yes, diagnosis_____________________   Lost - If yes, last Study day examined: _____________   Error made during follow-up that prevented outcome classification: ______________________________ |

| **UMSP clinical record form (1): Three-Arm Study (CQ/SP, AQ/SP, AQ/AS)** | | | | | | | | | |
| --- | --- | --- | --- | --- | --- | --- | --- | --- | --- |
| **Patient**  **Initials:** | **1. Study Number: U**|___|___|___|___|___| | | **2. Day 0 Date:** |___|___|/|___|___|/|___|___|  ***day month year*** | | | | | **3. Treatment Number:** |___|___|___| | |
| **4. Age:_______years______months**  *(include months only if age < 5 years, else write “X”)* | | **5. Gender: _____M _____F** | | | **6. Weight***(kg):* | **7. Known drug allergies: ___Yes ___No ___Unknown**  **If yes, describe___________________________________** | | | |
| **List all medications taken within the last 2 weeks** | | | | | | | | | |
| **Drug** *(if name unknown, list by letter – “Unknown Drug A”)* **(a)** | | | | **Dose** *(# of tablets/injections)* **(b)** | | | **Dates given (c)** | | **Duration (d)** |
| 8. | | | |  | | |  | |  |
| 9. | | | |  | | |  | |  |
| 10. | | | |  | | |  | |  |
| 11. | | | |  | | |  | |  |

| **symptom record**  ***(Rank on scale of 0-4: absent = 0; mild = 1; moderate = 2; severe = 3, life-threatening = 4, N/A = unable to assess)*** | | | | | | | | | | |
| --- | --- | --- | --- | --- | --- | --- | --- | --- | --- | --- |
|  | **day 0 (a)** | **day 1 (b)** | **day 2 (c)** | **day 3 (d)** | **day 7 (e)** | **day 14 (f)** | **day 21 (g)** | **day 28 (h)** | **day ---- (i)** | **day ---- (j)** |
| **DATE** |  |  |  |  |  |  |  |  |  |  |
| 12. Subjective fever  in past 24h *(Y/N)* |  |  |  |  |  |  |  |  |  |  |
| 13. Weakness |  |  |  |  |  |  |  |  |  |  |
| 14. Muscle/joint aches* |  |  |  |  |  |  |  |  |  |  |
| 15. Headache* |  |  |  |  |  |  |  |  |  |  |
| 16. Anorexia |  |  |  |  |  |  |  |  |  |  |
| 17. Nausea* |  |  |  |  |  |  |  |  |  |  |
| 18. Vomiting |  |  |  |  |  |  |  |  |  |  |
| 19. Abdominal pain* |  |  |  |  |  |  |  |  |  |  |
| 20. Diarrhea |  |  |  |  |  |  |  |  |  |  |

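### The protocol promises intention-to-treat, but excluded and lost patients get no primary outcome, so the primary comparison is in effect one of classified patients

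*Protocol*

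**What the plan says.** **Promised analysis.** Section 4.2.1: "Pair wise comparisons between regimens will be made on an intention-to-treat basis". Section 8.2: "Primary analyses will be conducted based on intention-to-treat and the primary analysis population will include all randomised subjects fulfilling selection criteria".

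**Endpoint.** Section 4.2.1: "Clinical outcome will be dichotomised into success (ACR) and failure (ETF or LTF"), assessed over 28 days. Section 8.2 compares dichotomous outcomes by chi-square or Fisher's exact test.

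**Removal after enrolment.** The subsection on exclusion and loss that follows section 7.3 says "Patients will be excluded from the study after enrolment if any of the following occurs". The first reason it lists is "Use of antimalarial drugs outside of the study protocol"; the second is "Development of concomitant febrile illness that may interfere with outcome classification"; the third is withdrawal of consent. Separately, the rule for a missed visit covers anyone whom staff do not find in time: "unable to be located within 24 hours on Days 1-3 or within 48 hours on Days 4-28 will be considered lost to follow-up".

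**Recording.** Form (4) in Appendix 15, in both the two-arm and three-arm sets, replaces the efficacy outcome of such a patient with N/A and sends the clinician to a box for incomplete outcomes. That box covers the three exclusion reasons, loss, and one more: "Error made during follow-up that prevented outcome classification".

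**Sample size.** Section 8.1 plans 160 per group for 15% versus 5% and 162 for 10% versus 2%, raised to 180 so that enough patients complete despite 10% loss.

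**The concern.** An intention-to-treat comparison needs a primary outcome, or a rule that stands in for one, for every patient in its population. Here a group of eligible randomised patients has neither. A two-by-two table of success against failure cannot hold them, so the denominator shrinks to those who could be classified.

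This is unlikely to be neutral. Appendix 3 counts fever or a history of fever with parasitaemia on Days 4 to 28 as late failure, and after Day 7 the scheduled visits are a week apart. A patient whose fever returns between visits and who takes an antimalarial elsewhere meets the exclusion rule before a failure can be recorded. That such patients are often failures is an inference, but a plausible one. If the trial's hypothesis is right, it would happen more often on CQ/SP.

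The absolute difference in failure and the power to detect it are at stake, in a trial whose results go directly to the Ministry of Health for drug policy (section 2.2).

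**Working it through.** **1. The sections side by side.** Sections 4.2.1 and 8.2 put every eligible randomised patient in the primary analysis. The exclusion and loss rules, with form (4), leave some of these patients with no efficacy code. The endpoint has no third category, and no section says how they count. The protocol can assign an outcome to incomplete treatment: sections 4.4 and 6.2 class repeated vomiting on Day 1 or 2 as treatment failure. No such rule exists for the patients discussed here.

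**2. Reproducing the planned sample size.** Inputs from section 8.1: two-sided α = 0.05, power 80%, equal groups. With p̄ the mean of the two rates and d their difference:

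n₀ = [1.96·√(2p̄(1−p̄)) + 0.842·√(p₁(1−p₁) + p₂(1−p₂))]² / d²

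n = (n₀/4)·[1 + √(1 + 4/(n₀d))]² (continuity correction)

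- 15% versus 5%: n₀ = 140.1, n = 159.5, so 160. Matches.
- 10% versus 2%: n₀ = 137.2, n = 161.2, so 162. Matches.
- Dividing by 0.90 gives 178 and 180, against 180 and 180 stated.

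The sample size arithmetic is sound.

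**3. Effect of excluding a share s of would-be failures.** The share is an assumption, taken as equal in both arms. The observed rate becomes

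p′ = p(1−s)/(1−ps)

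For s = 1/3: 0.15 × 0.667 / 0.95 = 0.105, and 0.05 × 0.667 / 0.983 = 0.034.

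Continuity-corrected power with n classified per arm uses n₀ = (n − 1/d)²/n and

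power = Φ{[√n₀·d − 1.96·√(2p̄(1−p̄))] / √(p₁(1−p₁) + p₂(1−p₂))}

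For s = 1/3 and n = 160: d = 0.0714, n₀ = 133.2, power = Φ(0.33) = 63%.

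| Share excluded | 15% vs 5% becomes | Difference (points) | Power, n = 160 | 10% vs 2% becomes | Power, n = 162 |
|---|---|---|---|---|---|
| 0 | 15.0% vs 5.0% | 10.0 | 80% | 10.0% vs 2.0% | 80% |
| 20% | 12.4% vs 4.0% | 8.3 | 71% | 8.2% vs 1.6% | 70% |
| 33% | 10.5% vs 3.4% | 7.1 | 63% | 6.9% vs 1.3% | 61% |
| 50% | 8.1% vs 2.6% | 5.5 | 50% | 5.3% vs 1.0% | 47% |

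Under equal shares the odds p/(1−p) are multiplied by (1−s) in both arms. The odds ratio therefore stays at 3.35 for 15% versus 5%, and the risk ratio rises slightly, from 3.00 to 3.11 at one third. Only the risk difference shrinks.

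**4. Unclassified patients against failures.** The planned loss is 10% of 180 = 18 per arm, leaving 162. Expected failures among those are 0.15 × 162 ≈ 24 on CQ/SP and 0.05 × 162 ≈ 8 on the comparator.

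- Counting all 18 as failures in both arms: 24/162 versus 8/162 (uncorrected chi-square p = 0.003) becomes 42/180 versus 26/180 (p = 0.031 uncorrected, 0.043 corrected or by Fisher's test).
- Extreme opposite handling, with all 18 successes on CQ/SP and all 18 failures on the comparator: 24/180 = 13.3% versus 26/180 = 14.4%, so the order reverses.

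**The case against.** The strongest defence is that the protocol excludes these patients from the study and never says from the analysis. Section 8.2 makes no exception for them, and a scoring rule for unclassified patients is often left to a statistical analysis plan, which is not at hand. It is true that no section orders them dropped, and an analysis plan could supply a rule. But the protocol does more than stay silent. It ends participation, prescribes a form that withholds the efficacy outcome, and defines an endpoint with no place for such patients. A later plan would have to work around those provisions.

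Three stronger readings are tempting, and the protocol does not support them.

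- A reader might infer that one missed visit removes a patient even if the patient returns later. The rule also requires that the patient could not be located, section 7.1 provides for home visits, and nothing is said about those who return.
- A reader might infer that the excluded patients are known failures. Late failure requires parasitaemia (Appendix 3), so self-treated fever without a smear does not meet the definition. Unscheduled visits, reimbursed transport and free care (sections 7.1 and 10.3) work against self-treatment, so the true share may lie below 20%.
- A reader might infer that counting the lost as failures overturns the result. In the worked example p stays below 0.05.

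The Day 1 exclusions for species or parasite density fit the population in section 8.2 and are not at issue.

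**Conclusion.** The point holds as an internal contradiction. The protocol claims an intention-to-treat primary comparison, but its exclusion rules, case record form and two-category endpoint together yield a comparison of classified patients. That conclusion rests on the text alone.

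The size is conditional. The losses of power in the table depend on an assumed share of failures excluded, equal in both arms, for which the protocol gives no figure. The bias is on the risk difference, which is the adjusted measure named in section 8.2, and not on the odds ratio. What needs no assumption about who self-treats is the scale: the planned loss of about 18 per arm exceeds the roughly 8 failures expected in the 5% arm. The handling of these patients can therefore matter as much as the events being compared.

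**What to change.** Reconcile sections 4.2.1 and 8.2, the exclusion and loss rules after section 7.3, and form (4) of Appendix 15.

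- **Primary set.** Keep all eligible randomised patients up to their last assessed visit. One workable method is a Kaplan-Meier 28-day failure risk in each arm and the risk difference, censoring at loss, withdrawal or exclusion. Another explicit rule would also serve, provided every patient in the set is accounted for.
- **Sensitivity analyses.** Count outside antimalarial use as failure. Apply best-case and worst-case handling to all unclassified patients, including those whose outcome was lost through a follow-up error. Counting self-treatment as failure belongs here and not in the primary analysis, because the Appendix 3 definition requires parasitaemia.
- **Secondary.** Report the proportion among classified patients, labelled as such.

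**Cost.** A little more analysis work. Censoring assumes that those removed have the same later risk as those who remain, which is doubtful for outside antimalarial use; the sensitivity analyses must probe it. The form needs an item for the date of and reason for outside antimalarial use, since it now asks only for a description and records the last day examined only for lost patients. For the others, the last assessed day can be derived from the visit dates.

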### 7.5. Pilot study:

A pilot study is planned prior to the onset of the actual study at each site. Approximately 10 pilot subjects shall be enrolled. They shall undergo all study procedures and will be followed for the full 28-day study period. A study group meeting will be held one week after beginning the pilot study to review all study procedures and assess for potential difficulties. We anticipate that actual study enrolment will begin 2 weeks after enrolling the pilot subjects.

### 8.0 STATISTICAL CONSIDERATIONS

### 8.1. Sample size calculations:

The sample size calculations will be made for each study based on the estimated efficacy of the combination regimens to be studied in the given region. For the purposes of sample size calculation, the risk of clinical failure at 28 days will be the main outcome. If the null hypothesis states that there is no difference in clinical outcome between the treatment groups, we plan to test the alternative hypothesis that treatment with an alternative combination regimen (AQ/SP or AS/AQ) will decrease the likelihood of clinical failure at 28 days of follow-up. Calculations will be made using an α = 0.05 and a statistical power of 80% based on a two-sided test. Allowance will be made for a possible 10% loss to follow-up to ensure that an adequate number of patients complete the study. Based on this, the sample size for the various drug combinations is summarized below:

Sample size for the different drug combinations

| **Presumed level of resistance.** | Resistance to CQ/SP | Resistance to AQ/SP or AS/AQ | Number per group | Number per group adjusted for loss to follow up. |
| --- | --- | --- | --- | --- |
| High resistance community (urban areas) | 15% | 5% | 160 | 180 |
| Low resistance community (rural areas) | 10% | 2% | 162 | 180 |

### 8.2. Analytical plan:

Data analysis will be primarily performed by the project statistician using EPI INFO, SPSS ACCESS and STATA statistical software packages, with additional assistance from members of the UCSF Epi-Center in San Francisco and the University of California, Berkeley, Department of Epidemiology. Primary analyses will be conducted based on intention-to-treat and the primary analysis population will include all randomised subjects fulfilling selection criteria.

Descriptive statistics will be used to summarise baseline characteristics of study patients. Parasite density values will be normalised using logarithmic transformation. All dichotomous variables will be compared between treatment groups using chi-square tests or Fisher’s exact tests. Continuous variables will be compared using t-tests. A p-value of < 0.05 will be considered significant.

Because age is a strong effect modifier in malaria, an age-stratified subgroup analysis for efficacy outcomes is planned. Study subjects will be stratified by age (< 5 years and > 5 years) for analysis of treatment outcome including clinical outcome at 14 and 28 days, and parasitological outcome at 14 and 28 days. Results for the two age groups will be presented independently. After calculating an estimate of association for each of the two age groups, a single adjusted measure of risk difference will be calculated. Other factors that may impact on antimalarial treatment outcome include temperature4 and mean parasite density at presentation ([name], unpublished data). Because a randomised trial is planned, we anticipate that known and unknown confounding factors will be equally balanced between the treatment groups. If by chance, there is an imbalance between the treatment groups for one or more potential confounding variables, adjustment will be made using multiple logistic regression.

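### Section 8.2 justifies the age analysis by effect modification, but no step compares the treatment effects in the two age groups

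*Protocol*

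**What the plan says.** Section 8.2 (Analytical plan) states its reason: "Because age is a strong effect modifier in malaria, an age-stratified subgroup analysis for efficacy outcomes is planned". Patients are split at 5 years, and clinical and parasitological outcomes at 14 and 28 days are analysed in each group. "Results for the two age groups will be presented independently". An estimate of association is calculated for each group, after which "a single adjusted measure of risk difference will be calculated".

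The section's general rule sends every dichotomous comparison between arms to a chi-square or Fisher's exact test, and "A p-value of < 0.05 will be considered significant". Logistic regression is mentioned only for adjusting chance imbalance in confounders.

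Section 8.1 sizes the overall comparison: "Calculations will be made using an α = 0.05 and a statistical power of 80% based on a two-sided test". The two rows of its table are "High resistance community (urban areas) | 15% | 5% | 160 | 180" and "Low resistance community (rural areas) | 10% | 2% | 162 | 180". Section 4.3 stratifies randomisation by the same two age groups. Neither section gives the expected age mix.

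**The concern.** Effect modification means that the treatment effect differs between younger and older patients. The matching null hypothesis is that the effect is the same in both groups. A within-group test has another null: no effect in this group. The pooled risk difference summarises the two effects as one number and does not examine whether they differ. So the section names a question and fixes a method that does not address it.

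This matters for how the results are read. Each age group holds only part of a sample sized for the whole, so one group can easily be significant and the other not when the benefit is the same in both. Section 2.2 says that the data go directly to the Ministry of Health for drug policy, where that pattern could be taken to mean that a regimen works in one age group only. Conversely, a real difference between the groups would be pooled without being estimated.

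**Working it through.** **Inputs from the protocol.** Two-sided α of 0.05, power 80%, failure risks of 15% v 5% and 10% v 2%, 160 and 162 per group (Section 8.1); two age groups (Sections 4.3 and 8.2); chi-square or Fisher at p < 0.05 (Section 8.2).

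**Assumptions.** Age split 50:50, with 70:30 as a variant. The same true risks in both age groups. One study analysed on its own, with pooling across sites as a variant.

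**1. Reproduce the stated sample size.** With d = p1 − p2 and p̄ the mean of the two risks:

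n = [1.96·√(2p̄(1−p̄)) + 0.842·√(p1(1−p1) + p2(1−p2))]² / d²

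n_c = (n/4)·[1 + √(1 + 4/(n·d))]² (continuity correction)

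- 15% v 5%: n = 140.1, n_c = 159.5, so 160.
- 10% v 2%: n = 137.2, n_c = 161.2, so 162.

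Both match. For "Allowance will be made for a possible 10% loss to follow-up", 160/0.9 = 178 and 162/0.9 = 180, consistent with the 180 in the table. The numbers therefore cover the overall comparison only.

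**2. Power within one age group at 50:50** (exact binomial enumeration).

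| Row | Per arm per age group | Chi-square | Fisher |
|---|---|---|---|
| 15% v 5% | 80 | 57% | 48% |
| 10% v 2% | 81 | 58% | 45% |

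**3. Chance that exactly one age group is significant.** With powers w1 and w2 it is w1(1 − w2) + w2(1 − w1).

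- 15% v 5%, chi-square: 2 × 0.573 × 0.427 = 0.489; Fisher: 2 × 0.481 × 0.519 = 0.499.
- 10% v 2%, chi-square: 2 × 0.576 × 0.424 = 0.488; Fisher: 2 × 0.451 × 0.549 = 0.495.

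**4. Variants.**

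| Setting | 15% v 5% | 10% v 2% |
|---|---|---|
| 70:30, chi-square | 54% | 54% |
| 70:30, Fisher | 58% | 61% |
| Two sites pooled, 50:50, chi-square | 23% | 19% |
| Three sites pooled, 50:50, chi-square | 7% | 5% |

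**5. Direct contrast of the two risk differences.** z = (RD1 − RD2)/√(sum of the four binomial variances). In simulated studies with the same benefit in both age groups, |z| > 1.96 occurs in 5.2% and 5.3% at 50:50, and in 5.5% and 5.7% at 70:30.

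**6. Power of that contrast** if the full planned effect is present in one age group and absent in the other.

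- 15% v 5%, 50:50: SE = √[(3 × 0.15 × 0.85 + 0.05 × 0.95)/80] = 0.0733. The difference to detect is 0.10, so 0.10/0.0733 = 1.36 and power is about 28%.
- 10% v 2%, 50:50: SE = √[(3 × 0.10 × 0.90 + 0.02 × 0.98)/81] = 0.0598. The difference is 0.08, so 0.08/0.0598 = 1.34 and power is about 27%.
- 70:30: simulated power is 23-26% across the two rows.

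**7. Why the scale must be named.** Suppose (assumed figures) the risk falls by 10 points in both age groups, from 20% to 10% in one and from 12% to 2% in the other. The risk differences are equal, but the odds ratios are (0.10/0.90)/(0.20/0.80) = 0.44 and (0.02/0.98)/(0.12/0.88) = 0.15. A logistic treatment-by-age term would then show an interaction where the risk-difference contrast shows none.

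**The case against.** The strongest reply is that the protocol never says effect modification will be judged by significance in one age group and not the other. It asks for an estimate in each group; within-group testing follows only from the general chi-square and Fisher rule. That stands. A reader might infer that the plan's own procedure finds spurious age effects many times more often than the nominal 5%. The document does not support this, because it states no such rule. The 49% describes what happens if someone compares p-values across the groups, which the text neither prescribes nor prevents.

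Second, the figure depends on inputs that the protocol does not settle. Section 4.4 assigns sentinel sites in the plural to each design, and Section 8.1 sizes each study, so it is not clear whether the age analysis is per site or pooled. Pooling lowers the figure; an unequal age split raises it. That stands too.

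Third, reporting age groups and then a pooled risk difference is not a contradiction, since the pooled value can be read as a weighted average. Granted: the tension with calling age a strong modifier is one of emphasis.

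Fourth, an interaction contrast is often left to an analysis plan. This carries less weight here. Section 8.2 itself fixes the age groups, the outcomes, the presentation and the pooled measure, and what it fixes does not address its stated reason.

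Last, the contrast would miss even a large difference about three times in four. That is a reason to report its interval, not to leave it out.

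**Conclusion.** The point holds as a gap in subgroup interpretation. Section 8.2 cites effect modification by age and fixes a method in which the two age-group effects are never compared. How often a uniform benefit would show as significant in exactly one group depends on an unstated age mix, on whether sites are pooled, and on a reader who compares significance across groups: about half of single-site studies at an even split, more at uneven splits, clearly less with pooled sites. A direct contrast keeps the false signal at about 5% in the single-study settings checked.

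A reader might go further and conclude that the main efficacy result or the sample size is unsound. It is not: the overall comparison in Section 4.2.1 and the numbers in Section 8.1 do not rest on the age analysis. This is a worthwhile, inexpensive improvement and not a flaw in the primary analysis.

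**What to change.** In Section 8.2:

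- Add the difference between the two age-group risk differences, with its 95% confidence interval and p-value. Name the risk-difference scale, to match the plan's pooled measure, and do not offer a logistic interaction term as interchangeable.
- Present each age group's result as a descriptive risk difference with a 95% confidence interval, and state that significance in one group only supports no age-specific conclusion.
- State that the overall or age-adjusted risk difference carries the conclusion.
- State that the contrast has low power (about 23-28% in the case above), so a non-significant result does not show equal effects and the interval is the main result.
- State whether the age analysis is done per site or pooled across sites.

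The cost is a few sentences and one contrast from data already collected. No patients, visits or measurements are added.
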